**Does a dependant or unequal relationship exist between the participant and the researcher?**

Please refer to the National Statement 4.3 for advice and guidance on how to manage this.

☐ Yes -

How will the dependant / unequal relationship be managed? [Click here to enter text.](#)

☒ No

### **Data management – as required in addition to that outlined in your HREA**

As per the National Statement 3.1.45, researchers must have a data management plan in place.

The Office for Research would like to remind researchers that the disposal of research records must be made in accordance with The State Records Act 1997 (the Act). Under that Act records must be disposed of as outlined in the general disposal schedules.

**Public health institutions** fall under general disposal schedule 28. As per item 6 of general disposal schedule 28, the researchers records of research including results, notes, completed questionnaires, signed consent forms, data, reports, and study findings must be kept for 15 years after the research project has been completed before being destroyed. This includes all types of research.

**Universities** fall under general disposal schedule 24. As per section 9 of general disposal schedule 24 research data records should be kept for a duration according to the nature of the study. For short term research projects such as study research projects, data should be kept for 1 year after last action. Research data from clinical trials should be kept for 15 years after action completed. All other research data and results should be kept for 5 years after publication, conclusion, or abandonment of the project. Data should be destroyed after the mandatory retention period.

Unless informed consent has been obtained from the participant, or legally authorised person, or the HREC has expressly approved otherwise, personal information used or disclosed for research purposes, must be de-identified. Only SA Health employees will perform the de-identification process prior to releasing the information for research purposes.

**Who will collect the study data / information?** Only SA Health employees can access patient data for research purposes. Students and non-SA Health employees cannot access patient records for research purposes under any circumstances.

The researchers will not access participants' data from hospitals for research purposes.

#### **Baseline demographic data and care service utilisation data:**

**SALHN and Resthaven SA:** The Flinders University employed researcher, [name], will collect baseline demographic data and a monthly care service utilisation data using RUD using the secured Flinders University online survey platform.

**Bolton Clarke Victoria:** [name] at the Bolton Clarke Research Institute will collect baseline demographic data and care service utilisation data.

**Canberra Health Services:** A researcher (name to be provided) employed by CI [name] will collect baseline demographic data and care service utilisation data.

#### **Self-administered survey:**

In addition to above data collection, participants will participate in online self-administered survey three times at baseline, 6 months and 12 months as part of data collection methods for the analyses of program effectiveness.

**Online care support group meeting data:**

The monthly online care support group meetings in the intervention group will be audio-recorded for data analysis to understand carers' experience in the iSupport program.

**Messages between participants and program facilitator:**

The messages (text messages via mobile, email and WhatsApp, request for support) and time spent by facilitator to provide the support will be documented and analysed.

**MBS and PBS data:** Will be provided by Services Australia, subject to their own approval process and requirements.

**What format will the data or information be stored?**

**Digital audio data format:** Data collected in the online carer group meetings, recorded/downloaded text messages and the voice recording of verbal consent are digital audio data. These types of data will be stored in a digital audio data format.

**Data in hard copy format:** The expression of interest and signed consent forms will be hardcopy data.

**Electronic data format:** The digital audio data from carer group meetings will be transcribed verbatim and the transcripts will be checked by researchers in each study site. Participants' identities will be removed from the transcripts before the data analysis. The de-identified transcripts will be stored in electronic format.

Online survey data without participant identities will be stored in an electronic data format.

Any data received from Services Australia will be stored in a password protected electronic folder on the Flinders University Research Drive. Only the PI [name] and the health economists [name] and [name] can access the folder to conduct the analysis or maintain proper governance and maintenance of the data files.

**Please provide details regarding training of the research team on maintaining the integrity and security of the data –**

The research team have relevant experience in maintaining the integrity and security of the type of data we will collect for this study. Prior to the study, all program facilitators researchers will attend an online training session to standardise data

collection and data analysis, and to comply with the study protocol and ethics requirements. PI [name] will lead the training session.

Strategies as listed below will be applied to maintain the integrity and security of the data:

- (1) The data will be verified and validated by two researchers to ensure the input is accurate.
- (2) The research team will secure the data with limited system access. For example, during the data collection and data analysis period, raw data will be in electronic format, have the unique codes for participants and be kept in password-protected electronic file. Only researchers in the project can access the data.
- (3) [name] will undertake monthly audits across study sites regarding the compliance with confidentiality of information and data storage.

#### **What conditions can the data be accessed or granted to others?**

De-identified online survey data in SPSS format, the transcripts of the online carer support group meetings and text messages will be shared amongst the research team only. No identifying information will be shared. No data received from Services Australia will be used for purposes outside this research project or provided to anyone outside of the research team.

#### **How will the research data be stored and what security measures are in place to protect it?**

##### **Digital audio data:**

The digital audio data collected from all study sites will be submitted to the PI [name] and will be stored securely on the Research Drive at Flinders University by the PI [name]. The data will not be shared within the project team, but for audit purpose.

##### **Electronic data format:**

The de-identified transcripts of online carer support group meetings and downloaded deidentified text messages will be stored in a password protected folder on the Flinders University Research Drive. This folder will be shared with all researchers in the project during this study phase for data analysis purpose. Once the data analysis has been completed, only the PI [name] can access the folder to maintain proper governance.

The online survey data will be downloaded and stored in an electronic data format in a password protected folder on the Flinders University Research Drive. Only the PI [name], CI [name] (biostatistician) and the researcher [name] can access the folder to conduct

the analysis. On the completion of this phase of study, only the PI [name] can access the folder to maintain proper governance. The site-specific CIs will scan the expression of interest and signed consent forms and store the scanned forms in an electronic data format in a password protected folder on the Flinders University Research Drive. Text messages will be downloaded as a On the completion of the data submission, only the PI [name] can access the folder to maintain proper governance.

The originals hard copy of the MBS and PBS consent form MUST be provided to Services Australia. The research [name] will scan the signed consent forms and store the scanned forms in an electronic data format in a password protected folder on the Flinders University Research Drive. Only the PI [name] can access the folder to maintain proper governance

Any data received from Services Australia will be stored in a password protected electronic folder, on a password protected Flinders University Research Driver. Only the PI [name], CI [name] and [name] can access the folder to conduct the analysis during this study phase. On the completion of this phase of study, only the PI [name] can access the folder to maintain proper governance or maintain proper governance and maintenance of the data files.

**Data in hardcopy format:**

The hard copy data collected by each study site will be stored in a secure locked filing cabinet in a particular room in a particular building approved by the organisation of the study site. Only the lead CI in each study site (PI [name] at Flinders University, CI [name] at Bolton Clarke Research Institute and CI [name] at Canberra Health Services) can access the data to maintain proper governance.

**How will you provide access to, disclose, use/re-use or transfer the data?**

Data will be analysed collectively in the project team. Therefore, de-identified data stored on the secured cloud of Flinders University Research Drive, will be used to access and share the data within the team members across multiple study sites during the study phase. To protect participants' identity, all sensitive (audio-recordings) and demographic information will be stored on the Research Drive and no access will be given to the broader research team. Participants will be assured that pseudonyms will be used in the reports and publications of the project.

**How long will the data be retained for?**

- ☒ The data will be kept for 15 years – for all SA Health research
- ☐ The data will be kept for 5 years – for all University research,

**What plans are in place to store / archive the study data once the research is completed?**

The Chief Investigator, [name], will maintain all records pertaining to this study for 15 years after publication according to the Australian Code for Responsible Conduct in Research. After 15 years, records will be destroyed according to the Government of South Australia General Disposal Schedule No. 24/30.

**What is the archive plan if the chief investigator leaves the institution and no longer has access to the study data?**

On the completion of the study, data will be stored on the Flinders University Research Drive which can be owner transferred to the associate investigator of the team by IT staff if the Chief Investigator, [name], leaves the institution and no longer has access to the study data.

**How will the study data be destroyed?**

All data will be retained for 15 years, and then it will be shredded to destroy permanently. Data stored electronically will be deleted from the Flinders University Research Drive and computer permanently by Flinders University IT services.

**Matching and sampling strategies:**

**Matching:**

Any information provided by participants will be collected in a de-identifiable form. Each participant and study site will be given a unique numerical code to represent their names on the data collection form throughout the project. The code will be used to match data generated from three-time surveys in the study.

**Sampling strategies**

After baseline data collection, carers will be randomly assigned to receive either the iSupport program group or the usual care group. To ensure the two groups are of equivalent size, a randomly generated block size of 4 will be used to allocate carers to one of the two treatment groups for each recruitment site. The randomisation will ensure equivalent distribution of spouse carers versus non-spouse carers and care recipients with mild versus moderate dementia in each treatment group.

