***Randomisation and interventions***

After baseline data collection, carers will be randomly assigned to receive either the iSupport program or the usual care. To ensure the two groups are of equivalent size and conditions, a block randomisation will be used to allocate carers to one of the two treatment groups for each recruitment site. Stratification will also be used in the block randomisation to ensure equivalent distribution of spouse carers versus non-spouse carers and care recipients with mild versus moderate dementia in each treatment group.

**Arm 1–Usual care group:** Carers will receive the usual carer support provided by Dementia Australia or other publicly funded carer support. They will receive a monthly reminder email that directs them to the Dementia Australia website where they can seek support if they wish.

**Arm 2–Intervention group:** The planned interventions are described in the following.

- (1) Managing transitions: In each study site, carers will be assigned to an iSupport program facilitator and encouraged to request individualised support from the facilitator during transition between care settings (i.e. from hospital to home transitional care) and types (i.e. receiving ambulatory geriatric services, or rehabilitation or palliative care at home in addition to usual home care package) of the PLWD.
- (2) Managing dementia progression: Carers are also encouraged to contact the facilitator to discuss changes in PLWD (i.e., signs of deterioration, changed behaviours and complications) and gain advice to access relevant multidisciplinary care services for timely treatment and care. The facilitator will follow the carers until their needs for support have been met.
- (3) Psychoeducation: Carers will select at least 20 out of 30 learning units that are relevant to them from the online iSupport program to learn over the first 6 months of the trial and revisit or learn new units when they feel it is needed in the second 6 months. The expected time spent on learning the online iSupport learning modules

is no more than 12 hours in total. The completion of each unit will be measured through the program design and will be recorded as data for compliance with the intervention. Carers will receive a certificate for each unit they complete, a strategy to motivate them in the program.

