**How many participants will be selected for the study?**

Based on sample size calculation, 184 carers in total. We plan to recruit 46 carers (23 in each arm) in each of the 4 study sites.

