**Exclusion criteria**

Carers will be excluded if they (1) have health conditions that may significantly impact their ability to participate in the study; (2) involve in other studies, and (3) cannot read English without additional assistance.

**Participant commitment** -What will their participation involve? I.e. study visits, procedures, tests, tissue samples, questionnaires, wearing of any devices.

**Arm 1–Usual care group:** Carers will receive the usual carer support provided by Dementia Australia or other publicly funded carer support. They will receive a monthly reminder email that directs them to the Dementia Australia website where they can seek support if they so wish. Carers will undertake an online survey (Appendix F) at three time points: baseline, 6 months and 12 months. They will be notified about each survey by email and an SMS message. Carer can reply 'stop' to indicate the termination of the reminder and withdrawing from the study. Each survey will take about 30 minutes. Carers will also undertake a monthly 10-minute survey to document the previous month health care services utilisation (Appendix G). Therefore, the time commitment for this group of carers would be no more than 9 hours.

**Arm 2–Intervention group:** Carers will engage in these activities:

- (1) Managing transitions: In each study site, carers will be assigned to an iSupport program facilitator and encouraged to request individualised support from the facilitator during transition between care settings (i.e. from hospital to home transitional care) and care types (i.e. receiving ambulatory geriatric services, or rehabilitation or palliative care at home in addition to usual home care package).
- (2) Managing dementia progression: Carers are also encouraged to contact the facilitator to discuss changes in PLWD (i.e. signs of deterioration, changed

behaviours and complications) and gain advice to access relevant multidisciplinary care services for timely treatment and care. The facilitator will follow the carers until their needs for support have been met.

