**Who will be confirming or renegotiating consent with participants and what process will be undertaken?**

**(1) SALHN and Resthaven SA sites:**

The researcher, [name] who obtained consent form from participants will be confirming or renegotiating consent with participants. She will send SMS to participants to remind them of each follow-up survey. She will also remind participants that they have the right to withdraw at any stage of the study. Participants can reply 'stop' to indicate the termination of the reminder and withdrawing from the study.

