**Accounting for potential bias, confounding factors and missing information:**

[name] who does not involve in participants recruitment will randomly assign participants (deidentified) into the intervention group and usual care group. This approach will account for potential bias.

Confounding factors will be controlled through statistical analysis design. In order to control the interference of the confounding factors on the research results and reduce the potential bias, univariate models will be first used, then multivariate modelling will be undertaken by adding variables considered clinically important or statistically significant from the univariate model to adjust for confounding effects between variables. A series of models will be undertaken by adding and subtracting variables, with changes in model fit assessed by log likelihood to choose the final multivariate model.

Data will be analysed on an intention-to-treat basis based on group assignments. For missing information in the data analysis, Mean/Model Imputation will be used to reduce the bias in missing data completely at random.

**Sample size and statistical or power issues** – Make sure the size and profile of the sample to be recruited is adequate to answer the research question – please provide details:

The sample size calculation is based on the primary outcome of the SF-12 mental component for carers and is estimated on the basis of an earlier RCT with similar intervention components for carers (Berwig et al., 2017). In that study, the SF-12 mental component for carers increased significantly by an effect size of 0.57 and standard deviation of 8.63. We assume that the same effect size would be observed in our trial. The estimated sample size would be 66 carers per arm using a 2-sample comparison of means for  $\alpha=0.05$  at 90% of power. The Welch-Satterthwaite t-test is used to calculate the sample size for unequal variances. Assuming an attrition rate of 40%, the estimated sample size would be 184 carers in total or 92 per group. A stata code power was used to calculate the sample size. Our investigation indicates that each industry partner provides care services for more than 500 persons with dementia annually and more than 80% of carers use email to communicate with care staff which will ensure sufficient numbers of carers recruited into the study.

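### One disclosed block size of 4 within small strata could let a recruiter who sees earlier allocations deduce up to about 30% of assignments

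*Protocol*

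**What the plan says.** Under *Sampling strategies* the Protocol states that "a randomly generated block size of 4 will be used to allocate carers to one of the two treatment groups for each recruitment site". Under *Randomisation and interventions* it adds: "Stratification will also be used in the block randomisation to ensure equivalent distribution of spouse carers versus non-spouse carers", with mild versus moderate dementia as a further factor. On numbers: "We plan to recruit 46 carers (23 in each arm) in each of the 4 study sites".

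On sequence: "After baseline data collection, carers will be randomly assigned to receive either the iSupport program or the usual care". On who allocates, under *Accounting for potential bias, confounding factors and missing information*, it names a person "who does not involve in participants recruitment will randomly assign participants (deidentified) into the intervention group and usual care group".

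The only person described as blinded is the research assistant who analyses the data (*Measuring the effectiveness of the iSupport program*). In the section on confirming or renegotiating consent, the researcher "who obtained consent form from participants will be confirming or renegotiating consent with participants" and also sends the reminders for follow-up surveys. The entries for Bolton Clarke and Canberra give the same arrangement. That researcher also assesses eligibility before taking consent (section on which investigators will obtain consent).

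One exclusion criterion calls for judgement: carers are excluded if they "have health conditions that may significantly impact their ability to participate in the study".

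**The concern.** In permuted blocks, the last one or two places are fully determined by the places already filled. If the block size is a single known number, anyone who can see the earlier assignments in a stratum can work out those last places. An independent allocator does not prevent this, because the deduction uses past assignments and not the list.

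Several features of this trial make such sight of past assignments plausible. The arms look different: a facilitator, online meetings and a messaging group on one side, a monthly reminder email on the other. The researcher who screens and consents stays in touch with carers afterwards. Site researchers also collect service-use data, and *Measuring the cost-effectiveness of the iSupport program* describes this as a monthly interview. The section on managing conflicts of interest says that site-specific researchers who collect data hold the record linking names to codes.

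Eligibility and consent come before randomisation. A recruiter who foresees the next arm could therefore be influenced, knowingly or not, in a borderline eligibility decision or in when a carer is put forward. The primary outcomes are reported by the carer, for the carer and by proxy for the care recipient, so a difference between arms in who was enrolled could carry through to the result.

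**Working it through.** **Inputs from the Protocol.** Block size 4; two arms of equal size; 4 sites with 46 carers each, 184 in total; two further binary factors. The Protocol gives no predictability figure to reproduce.

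**Strata.** 4 × 2 × 2 = 16, and 184/16 = 11.5 carers on average.

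**Forced places in a complete block.** There are 6 equally likely balanced blocks. In 2 of them (AABB, BBAA) the third and fourth places are forced. In the other 4 only the fourth is forced.

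- Expected forced places: (2/6 × 2) + (4/6 × 1) = 4/3 per block.
- Share: (4/3)/4 = 33.3%.

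**Allowing for incomplete last blocks.**

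- Stratum of 12: 3 × 4/3 = 4 forced places.
- Stratum of 11: two full blocks plus three places of a third, in which the third place is forced with probability 2/6. That is 4/3 + 4/3 + 1/3 = 3.
- Eight strata of each size (8 × 12 + 8 × 11 = 184): (8 × 4 + 8 × 3)/184 = 56/184 = 30.4%.
- Simulation with each site's 46 carers falling at random into its four cells: 29.8%, or 0.298 × 184 ≈ 55 carers. Uneven cells (0.4, 0.3, 0.2, 0.1) give 29.7%.
- Single strata of 8 to 15 carers range from 27% to 33%.
- If blocks ran by site only: 46 = 11 full blocks + 2 places, so (11 × 4/3)/46 = 31.9%.

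**Best guess, complete block.** The chance of guessing each place correctly is 1/2, 2/3, 2/3 and 1. The mean is (0.5 + 0.667 + 0.667 + 1)/4 = 70.8%. Over the 16 strata with incomplete blocks it is 69%. Pure chance is 50%.

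**Varying sizes.** Same 16 strata with equal cell probabilities, and a guesser who knows the set of possible sizes and all earlier allocations in the stratum and updates by Bayes' rule:

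| Block sizes | Known with certainty | Best guess correct | Largest imbalance in a stratum |
|---|---|---|---|
| 4 | 29.8% | 69% | 2 |
| 4 and 6 | 6.1% | 68% | 3 |
| 4, 6 and 8 | 2.2% | 66% | 4 |

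The largest imbalance is half the largest block, reached when a stratum closes midway through it.

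**Lower end.** A recruiter who sees no earlier allocations can deduce none, so certain knowledge is 0%.

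**The case against.** The strongest reply is that all of this is conditional. The Protocol nowhere says that recruiters are told allocations. Survey reminders and consent checks need not reveal the arm. The main surveys are online and self-administered, and at SALHN and Resthaven the service-use data are collected through an online platform. This stands: learning the arms is likely but not documented. A reader might infer that the recruiting researcher will know a third of allocations in advance. The text does not support that; it supports only a range from 0% to about 30%.

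Second, the list itself is protected. Someone outside recruitment allocates de-identified participants. A reader might infer that allocation is unconcealed, and that would be wrong. What remains open is deduction from past assignments.

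Third, between screening and randomisation come a consideration period of at least 24 hours (up to 3 or 7 days, depending on the section), consent and a baseline survey that the carer completes. Others in the stratum may be randomised meanwhile, so the recruiter may not know a carer's exact place in the block. This makes steering harder but does not rule it out.

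Fourth, the model adjusts for the baseline value of the outcome. That removes the part of any selection bias that acts through the measured baseline score. Selection on unmeasured traits, such as motivation, would remain.

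Fifth, the phrase about a randomly generated block size of 4 is awkward. A single fixed size is its natural reading, since no other size is named, but it is still a reading.

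Finally, varying the sizes hardly changes best-guess accuracy. This also stands: the gain is in removing certainty.

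**Conclusion.** The point holds as a conditional weakness of the randomisation design. The Protocol discloses one block size, applies it in small strata of a trial in which only the analyst is described as blinded, and sets no barrier between the recruiting researchers and earlier allocations. Up to about 30% of assignments (about 55 of 184) could be deduced with certainty, or 33% if every block is complete.

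This ceiling assumes that the block size is fixed at 4, that the strata are the 16 site × spouse × severity cells, and that the recruiter knows the stratum and every earlier allocation in it. Reading the blocks as site-only changes it little (31.9%). If earlier allocations stay hidden, it is 0%.

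The documents do not show that selection will occur, and they give no basis for putting a size on any resulting bias in the treatment effect. The change is worth making because it is nearly free.

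**What to change.** Replace the single size with permuted blocks of randomly varying size (for example 4 and 6, or 4, 6 and 8). State that the sizes are held only by the independent allocator, and remove them from documents that the sites see. Where existing roles allow, add that researchers who screen and consent are not given the running allocations. This second step acts directly on the mechanism, because varying the sizes leaves best-guess accuracy almost unchanged.

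The cost is a regenerated randomisation list and a slightly larger possible imbalance within a stratum: 3 with sizes 4 and 6, or 4 with sizes 4, 6 and 8, instead of 2. If recruitment has begun, the change can apply to blocks not yet started.

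The stratification names only mild and moderate dementia, although eligibility sets no upper severity limit. That is a separate matter and should be raised on its own.
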